### The intervention program

A conceptual model was developed for designing individually tailored programs termed “Intelligent Physical Exercise Training”, IPET. The concept of IPET at the worksite was: 1) to balance the physiological capacity of the employees relative to occupational exposure, 2) to tailor the exercise to individual capacities and disorders to improve employees’ health, 3) to motivate participants by offering evidenced and enjoyable programs implemented with care, and 4) to be cost-effective for the company.

**Ad 1)** The occupational exposure was sedentary work with intense computer use for all eligible participants in this study. This implied that inactivity had to be reduced by following the guidelines from American College of Sports Medicine [1]. To reach these targets in quantity it was negotiated with employees and top-management that 1 hr of vigorous intensity training (77 – 95%HRmax, RPE 14–17) per week would be performed during working hours and 30 min moderate intensity training (64–76%HRmax, RPE 12–13) six days a week during leisure by each participant or a minimum of 3 hrs per week. The instructors were supervising the 1 hr vigorous intensity training at facilities in the workplace or in the local area one day a week during the first year; during the second year they supervised only 1 hr a month. The health ambassadors were active in advising and motivating for the leisure time training, mainly dynamic activities using large muscle groups (64–76%HRmax)

**Ad 2)** The health check and musculoskeletal check as well as questionnaire served to tailor the activities to the individual for the high intensity training 1 hr a week at the worksite. The training was composed of the 3 major training categories: Cardio-respiratory fitness, strength training, and functional training (or neuromuscular training). The latter two were subdivided into strength training for neck/shoulder or large muscle groups, and functional training for core stability or balance, respectively, resulting in 5 different categories to allocate training duration for (see Table 1). Specific cut-points were set from the health check measures for recommending a specific training category (see below). Additionally, questionnaire reply (see below) of musculoskeletal complaints for > 30 days/year in neck/shoulder or low back resulted in recommending training of neck/shoulder strength and functional core stability training, respectively. Likewise, the musculoskeletal check could result in recommended training of neck/shoulder strength and functional training of torso and/or balance. Depending on the number of recommended training categories (max 5) the time allotted to these exercises was adjusted according to Table 2. Several cut-points often qualified for recommending the same training category, but the time allocated to the five different training categories was independent of the number of tests surpassing a cut-point.

**Ad 3)** Instructors as well as health ambassadors were recruited to assist the participants and spur their motivation (see above). Further, each employee received a hand-out with an individual intelligent physical exercise training program. All training sessions lasted 50 min – allowing 10 min for getting to and from the site of work and the site of training within the one hour off work – and were led by instructors. Of these sessions always 20 min were in the beginning allocated to cardio-respiratory fitness training, including 10 min warm-up, due to the physical inactivity at the job. After this the instructor guided each employee to train their specific exercises and at recommended training intensities. Those employees who did not surpass any of the cut-points for recommending specific training categories were to train 25 min cardio-respiratory fitness and 25 min strength training for large muscle groups while all others had specifically composed training categories (Table 2).

Exercises for cardio-respiratory training were up to the employee to choose with guidance from instructors and with the focus on training at high intensity and could be running, stepping, rowing, ball games etc. Exercises for strength training of large muscle groups were selected from 5 different exercises: 1 for shoulders, 3 for abdomen-back and 1 for the breast muscles. The intensity for strength training of large muscle groups was 60 – 80% of one repetition maximum, RM. Frequency: 3 sets of 8 repetitions. Breaks: Employees were instructed to shift between exercises, which meant maximum 10 s breaks between sets. Exercises for neck and shoulder strength were shrugs, reverse flyers, and arm abduction, i.e. evidenced previously to increase strength/endurance and reduce neck/shoulder pain [17,38]. The intensity for neck and shoulder training was to pain limits or as heavy as possible and with proper technical execution. Frequency: 3 sets of 8 repetitions. Breaks: 1 – 2 min breaks between sets. Exercises for functional training were selected from 9 different exercises: 5 for balance training and 4 for core stability training. Functional training had no demands for intensity or frequency.

**Ad 4)** Measures of sickness absence recorded by the company and responded to the questionnaire by the employer together with their data on salary and self-reported productivity and workability will feed into models of health economics [14]. Account will be taken on the hours of training during working hours.

**Table 2 T2:** **All possible combinations of the five training categories in Table **1** and the time (minutes) allotted to each category for each combination**

**Number of exercise categories**	**Combination of exercise categories (*)**	**Cardio (Ca)**	**Extra cardio**	**Neck/Shoulder (NS)**	**Large Muscles (LM)**	**Core Stability (CS)**	**Balance (Ba)**	**Combi- nations used**
**0**		20	5		25			
**1**	**Ca**	20	5		25			21
	**NS**	20		20	10			1
	**LM**	20	5		25			
	**CS**	20	5		5	20		
	**Ba**	20	5		20		5	
**2**	**Ca + NS**	20	5	20	5			17
	**Ca + LM**	20	5		25			
	**Ca + CS**	20	5		5	20		2
	**Ca + Ba**	20	5		20		5	
	**NS + LM**	20		20	10			3
	**NS + CS**	20		20		10		12
	**NS + Ba**	20		20	5		5	1
	**LM + CS**	20			15	15		
	**LM + Ba**	20	5		20		5	
	**CS + Ba**	20			10	15	5	
**3**	**Ca + NS + LM**	20		20	10			17
	**Ca + NS + CS**	20		20		10		33
	**Ca + NS + Ba**	20	5	20			5	6
	**Ca + LM + CS**	20	5		15	10		16
	**Ca + LM + Ba**	20	5		20		5	3
	**Ca + CS + Ba**	20	5			20	5	1
	**NS + LM + CS**	20		15	5	10		16
	**NS + LM + Ba**	20		15	10		5	
	**NS + CS + Ba**	20		15		10	5	7
	**LM + CS + Ba**	20			15	10	5	
**4**	**Ca + NS + LM + CS**	20		15	10	5		18
	**Ca + NS + LM + Ba**	20		15	10		5	1
	**Ca + NS + CS + Ba**	20	5	15		5	5	15
	**Ca + LM + CS + Ba**	20	5		10	10	5	1
	**NS + LM + CS + Ba**	20		15	5	5	5	
**5**	**Ca + NS + LM + CS + Ba**	20		10	10	5	5	3

(*) Ca: Cardio training, NS: Neck/shoulder strength training, LM: Large muscle groups strength training, CS: Core stability functional training, and Ba: Balance functional training.

Last column shows the number of participants who were allocated to the combination at baseline.

### Outcome measures

#### Objective measures

Measures obtained during the health check were:

##### Estimated maximal oxygen uptake (VO_2max_)

VO2 max was the primary outcome for this study and was estimated from the relation between sub-maximal workload and steady state heart rate obtained in Åstrand one-point sub-max test using the Åstrand nomogram [39] and correcting for age [40]. The tests were performed on a bicycle (Monark 874E, Monarch Exercise AB, Sweden) and with heart rate (HR) measured (Polar S610i Heart Rate Monitor and Polar FT2 Heart Rate Monitor). Test procedure: The starting load was 60 Watt for women and 90 Watt for men pedaling at 60 rpm. After 2 min of warm-up the load was adjusted based on the measured HR. If the HR was below 120 beats per min (bpm) the load was adjusted with 30 Watt every minute until a steady state HR (change of ≤ 4 bpm per 1 min) was reached between 120 – 170 bpm. The test length was maximum 10 min and employees were instructed not to talk during the test. The cut-point for recommending extra cardio-respiratory fitness training was a test value <80% of the reference value from the Danish working population [41].

##### Muscle strength

Maximal isometric muscle strength was measured with Bofors MODEL dynamometer (Bofors Elektronik, Karlskoga Sweden) mounted in a reproducible standardized setup for 4 tests: Shoulder elevation, arm abduction, back extension, and abdominal flexion. In every test the employees completed 3 maximal voluntary contractions (MVC) with at least a 30 s break between tests (if the 3^rd^ MVC was 5% higher than the first and second test the employee was instructed to perform another test with the maximum of 5 tests). The highest value was recorded and moment arm for all test was registered [42]. The cut-point for recommending strength training was a test value for a particular body region <80% of the reference value from the Danish working population [41].

##### Balance test

A unilateral stance test was performed with eyes open and participants were instructed to look directly ahead at a black spot placed approximately 2 meters in front of them at eye height. The participants stood on the dominant foot (defined as the foot used for standing while kicking a ball) with the big toe of the non-dominant foot leaning against the medial malleolus of the dominant foot. The test was performed for 30 s [43]. Each participant was allowed three trials with loss of balance before the end of the test being classified as failed. The cut-point for being allocated to balance training was failure of all three trials.

##### BMI and body fat

Body height, weight, and fat were measured using a bio impedance device (Tanita TBF 300). Employees were normally hydrated and were measured without shoes and socks and with light clothing. Waist/hip ratio was measured with a ruler [44]. The cut-points for recommending cardio-respiratory training were: BMI ≥ 25 or fat% >24 to >44% depending on age and sex [45].

##### Blood pressure

Blood pressure was measured in seated position after 5 – 10 minutes of rest. Blood pressure was measured on the right arm with an electronic blood pressure device (OMRON M7). Blood pressure was measured 3 times with one minute rest between tests and the mean of the 2 lowest values was calculated [46]. The cut-point for recommending cardio-respiratory training was diastolic pressure > 90 mmHg or systolic pressure > 140 mmHg.

##### Blood profile

On the health check day overnight fasting blood samples (>7 hrs) were taken between 07:00 – 09:00 am. Blood samples were handled by technical personal from The University of Southern Denmark. The cut-points for recommending cardio-respiratory training were: Blood sugar ≤ 4 or ≥7 mmol/l, blood triglycerides ≤ 2 mmol/l, total cholesterol ≥6 mmol/l, LDL ≤ 3 mmol/l, and HDL ≥ 1 mmol/l.

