**Physiological health check**					
Aerobic fitness test	X				
Body mass index (BMI)	X				
Body fat%	X				
Blood pressure	X				
Blood fat (LDL + HDL)	X				
Blood glucose	X				
Balance test					X

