### Impact of results

The conceptual model presented here is easily applicable for practical use. If proven effective, the intelligent physical exercise training scheduled as well as the information for its practical implementation can provide meaningful scientifically based information for public health policy and health promotion strategies for employees in job groups at high risk for physical inactivity. This knowledge can be beneficial for occupational health professionals, supervisors, companies and employees in these job groups. Because the interventions are carried out during ordinary circumstances at a wide range of Danish workplaces, it is expected that the findings can be transferred and interventions implemented in other workplaces with high physical demands.

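### The triglyceride, LDL and HDL cut-points for cardio training are printed on the favourable side, so the published tailoring rule is very probably not the one that produced Table 2

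*Protocol article*

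**What the plan says.** The section Blood profile (Outcome measures) opens its list with "The cut-points for recommending cardio-respiratory training were: Blood sugar ≤ 4 or ≥7 mmol/l" and continues with "blood triglycerides ≤ 2 mmol/l, total cholesterol ≥6 mmol/l, LDL ≤ 3 mmol/l, and HDL ≥ 1 mmol/l". The opening words make these values triggers for training, not health targets.

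The other cardio triggers are given in neighbouring sections. Estimated VO2max triggers below 80% of the reference value. BMI triggers from 25 upwards, and body fat above an age- and sex-specific limit. For blood pressure the text is "The cut-point for recommending cardio-respiratory training was diastolic pressure > 90 mmHg or systolic pressure > 140 mmHg".

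On how the cut-points combine, The intervention program (Ad 2) says "Several cut-points often qualified for recommending the same training category", and adds that the time given to a category does not depend on how many tests crossed their limit. Ad 3 sets a floor: "Of these sessions always 20 min were in the beginning allocated to cardio-respiratory fitness training".

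Table 2 lists the minutes for each combination of training categories. Its footnote reads "Last column shows the number of participants who were allocated to the combination at baseline". Under Impact of results the article states: "The conceptual model presented here is easily applicable for practical use".

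**The concern.** High triglycerides, high LDL and low HDL are the adverse directions. This is general clinical knowledge and needs no outside figure. The article prints the reverse for all three, while total cholesterol in the same list points the adverse way. No visible text corrects the signs.

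The cut-points are the operative part of the tailoring model that the article sets out to publish. A workplace copying them would recommend cardio training on the basis of good lipids. It would not flag on lipids a person with high triglycerides, high LDL and low HDL unless total cholesterol also reached 6. If the printed rule had been applied in the trial, almost everyone should have been flagged for cardio. Table 2 does not show that.

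**Working it through.** **1. Direction of each cardio trigger, as printed**

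| Measure | Printed trigger | Side |
|---|---|---|
| Estimated VO2max | <80% of reference | adverse |
| BMI | ≥25 | adverse |
| Body fat | above age/sex limit | adverse |
| Blood pressure | >140 or >90 | adverse |
| Glucose | ≤4 or ≥7 | two-sided |
| Total cholesterol | ≥6 | adverse |
| Triglycerides | ≤2 | **favourable** |
| LDL | ≤3 | **favourable** |
| HDL | ≥1 | **favourable** |

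Reading the list as targets instead of triggers does not rescue it: total cholesterol ≥6 and glucose ≤4 or ≥7 would then be the wrong ones. A joint reading (all lipid conditions needed together) conflicts with Ad 2, where several cut-points can each qualify a person for the same category.

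**2. Table 2, last column**

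- With cardio (Ca): 21+17+2+17+33+6+16+3+1+18+1+15+1+3 = 154.
- Without Ca: NS 1 + NS+LM 3 + NS+CS 12 + NS+Ba 1 + NS+LM+CS 16 + NS+CS+Ba 7 = 40.
- Total 194. With Ca 154/194 = 79.4%. Without Ca 40/194 = 20.6% (exact 95% CI 15.2% to 27.0%).

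These counts reproduce the article's Discussion. Cardio at 79.4% and neck/shoulder at 150/194 = 77.3% fit its figure of around three quarters. The nine combinations with 12 or more participants hold 165/194 = 85.05%, which fits its figure of more than 85%.

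**3. What the printed rule implies for the 40**

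Each would need triglycerides >2, LDL >3 and HDL <1 together, with total cholesterol <6, BMI <25 and normal fat, blood pressure, glucose and fitness. Let p be the share of participants with that whole profile. The documents give no lipid distribution, so p is an assumption. With X ~ Binomial(194, p):

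| Assumed p | Expected unflagged (194 × p) | P(X ≥ 40) |
|---|---|---|
| 1% | 1.9 | 1.2e-39 |
| 5% | 9.7 | 2.2e-14 |
| 10% | 19.4 | 8.0e-6 |
| 15% | 29.1 | 0.021 |
| 20% | 38.8 | 0.44 |

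p cannot exceed the smallest of the three single lipid prevalences. It reaches that ceiling only if the three abnormalities overlap fully and everyone concerned passes all other cardio tests. If the three were independent, with assumed prevalences from 0.10 × 0.05 × 0.50 = 0.0025 to 0.30 × 0.25 × 0.70 = 0.0525 (triglycerides, HDL, LDL), only 0.5 to 10.2 people would be unflagged.

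With the three signs reversed, a rough calculation on assumed shares crossing the BMI, LDL and remaining cut-points gives an unflagged share between 0.55 × 0.40 × 0.70 = 15% and 0.70 × 0.70 × 0.80 = 39%. The observed 20.6% lies inside. That shows compatibility, not proof.

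**4. Effect on programmes if all 40 had been flagged**

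| Actual combination | n | Change when Ca is added (minutes) |
|---|---|---|
| NS+CS | 12 | none |
| NS+LM | 3 | none |
| NS+LM+CS | 16 | LM +5, CS −5 |
| NS | 1 | cardio +5, LM −5 |
| NS+Ba | 1 | cardio +5, LM −5 |
| NS+CS+Ba | 7 | cardio +5, CS −5 |

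So 15 programmes are identical, 16 keep the same cardio time, and 9 (9/194 = 4.6%) gain 5 minutes of cardio per session.

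**The case against.** The strongest reply is that this is a reporting slip with little consequence. Every session already has 20 minutes of cardio, leisure training comes on top, and the flag adds at most 5 minutes. Enrolment ran from May 2011 to March 2012, so programmes had been assigned before publication. A health professional would notice reversed LDL and HDL limits, and the remaining cardio tests would still flag many people. All of this stands, and it limits the point to reproducibility of the intervention.

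Three further objections have weight. The tail probabilities rest on assumed prevalences, and near 20% the observed count is unremarkable. So Table 2 supports the inference but cannot prove it; the direction error stands without it. The replacement values are not in the article, so the defensible request is for the rule actually used. And Figure 2, which relates health check variables to training categories, is not shown, so it can only be said that no visible text corrects the signs.

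What does not stand is dismissing this as cosmetic. These are decision thresholds of a tailored intervention, in an article written to let others apply it.

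**Conclusion.** The concern holds. Three of the four lipid cut-points are wrong as written: they contradict all other one-sided cardio triggers, and no single reading makes the list consistent. The printed rule is very probably not the one behind Table 2, since it would require about one in five office workers to combine three adverse lipid values with otherwise normal cardio tests. This is a judgement of plausibility, because the article reports no lipid data. A misprint is likelier than a misapplied rule.

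The size within the trial is small: at most 9 of the 40 participants not recommended cardio would have had more cardio time. Randomisation, the VO2max endpoint and the between-group analysis do not depend on these signs. The error should be fixed because it misstates the intervention to those who would reuse it.

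**What to change.** Replace the three inequalities under Blood profile with those actually applied, presumably triglycerides ≥2, LDL ≥3 and HDL ≤1 mmol/l. Run the corrected rule once on the stored baseline data and confirm that it returns 154 flagged and 40 not flagged. This also settles whether the rule was misprinted or misapplied. In the same correction, align the blood-fat row of Table 1, which names only LDL and HDL, with Blood profile, which also uses triglycerides and total cholesterol; this last item is minor.

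The cost is a short published correction and one check of existing data. No allocation, endpoint or analysis changes.

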#### Self-reported measures

##### Questionnaire

All employees completed a questionnaire three times: at baseline as well as after one and two years of intervention. Questions addressed: demographics, education, job, income before tax, productivity [26], workability [27], psychosocial aspects [47], pain/kinesiophobia, self-rated health [48], sick leave, smoking, alcohol, physical activity at leisure [49], and sports activities specified as: ball games, Nordic walking, jogging, cycling, aerobics, spinning, dancing, swimming, kayaking/rowing. Questions regarding musculoskeletal disorders were assessed by a modified version of the Nordic questionnaire of musculoskeletal disorders [50]. Cut points for recommending strength training for neck/shoulder or functional training for core stability were > 30 days complaints during the last year in the neck/shoulder area and low back area, respectively. At follow-up after one and two years, respectively, questions regarding adherence as well as the impact of the health ambassadors were included. Their impact was rated from 1 for no impact to 10 for major impact.

##### Diary

Employees in the training group reported every week to the health ambassador regarding their physical activity at leisure. The reports were categorized into: Running, organized fitness training, strength training, home & gardening, climbing stairs. The total time for activity as well as time with moderate and high intensity, respectively was inquired.

#### Report by instructor

The instructors filled in a training diary with attendances and intensity of training in terms of RPE for employees in the training group for each 1 hr weekly scheduled training sessions.

#### Company registered data

Each company delivered their records of sickness absence for all employees included in the study for three years: the year before baseline measures, as well as first and second year of intervention.

### Statistics

All results are reported as mean (SD) and p < 0.05 is considered statistically significant. Primary and secondary outcomes will be analyzed within (paired t-test) and between the intervention group and the control group after intervention (ANCOVA). Categorical variables will be tested using chi-square and McNemar tests. Analyses will be performed using SPSS statistical software, version 21. Intention to treat analyses will be performed and values carried forward and backwards for missing values in both baseline and follow up measurements. If measurements have missing values in both baseline and follow up they will be replaced by means of all existing data in each group, respectively. Per-protocol analysis will be carried out with employees from the training group who meet the criteria of at least 70% adherence in the training period [51]. Sample size calculation is based on a 5% improvement in VO_2max_ on a group level with a SD of 20%, type 1 error of 5% and a power of 80% which showed a requirement of 128 employees in each group [52]. With an estimated dropout of 30% the research project has to recruit around 400 employees.

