#### Health check

Participants had scheduled a one hour health check at baseline before the intervention and at follow up after one and two years of intervention. Measurements included were: VO_2max_, muscle strength, body mass, body height, body fat percent, waist/hip ratio, blood pressure, blood lipid and glucose profile. Additionally a balance test was performed. All employees received individual notification shortly after the checks. Cut-points for recommending specific training modes are given in the section “Outcome measures”, see also Table 1.

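### Within-arm paired tests share the p < 0.05 threshold with the between-arm ANCOVA, and nothing says that the ANCOVA decides the hypotheses

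*Protocol article*

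**What the plan says.** The trial is a two-arm, parallel-group, individually randomised comparison of the training programme (IPET) with a control group (Study design). Estimated VO2max, a continuous measure, is the primary outcome (Outcome measures).

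On analysis, the Statistics section says: "Primary and secondary outcomes will be analyzed within (paired t-test) and between the intervention group". The same sentence goes on to name ANCOVA as the test of the two arms against each other. For categorical outcomes: "Categorical variables will be tested using chi-square and McNemar tests". One threshold covers everything: "All results are reported as mean (SD) and p < 0.05 is considered statistically significant". The section does not rank the within-arm and between-arm tests, and it does not call the within-arm tests descriptive.

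The four hypotheses, in the Abstract and at the end of the Background, are worded as improvement, decrease or reduction (the third as success in adherence). None mentions the control group.

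The sample size assumes that VO2max rises by 5%, with 20% as its SD. The article then gives the remaining inputs and the result: "type 1 error of 5% and a power of 80% which showed a requirement of 128 employees in each group". It is not said whether the 20% is the SD of VO2max itself or of its change, or whether the 5% is a difference from control.

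**The concern.** Randomisation protects the comparison between arms. It does not protect the comparison of an arm with its own baseline. Anything that moves both arms together, such as familiarity with the cycle test, a secular change, or a reaction to the health check, enters the paired test as if it were a training effect. The documents contain one such shared exposure: "All employees received individual notification shortly after the checks", which includes the controls.

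Because a hypothesis of improvement can be met, as worded, by a significant paired test in the IPET arm, the text leaves open a claim of benefit from a test that ignores the control group. A report that the training arm changed significantly and the control arm did not would have the same fault, since that pattern is not a test of the difference between arms.

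**Working it through.** **1. The plan's own sample size.** Inputs from the Statistics section: improvement 5%, SD 20%, type 1 error 5% (two-sided assumed; the article does not say), power 80%. Standardised effect d = 5/20 = 0.25.

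- Paired (one-sample) test, normal approximation: n = (1.960 + 0.842)² / d² = 7.849 / 0.0625 = 125.6, so 126. The exact t calculation gives 127.5, so **128** (power 0.798 at 127 and 0.802 at 128). The stated figure is reproduced.
- Plain two-arm comparison: n per arm = 2 × 7.849 / 0.0625 = 251.2, so 252 (exact t: 253). With 128 per arm the power is about 51%.
- ANCOVA, if 20% is the cross-sectional SD and ρ is the correlation of baseline with follow-up: n per arm = 251.2 × (1 − ρ²). This gives 189 at ρ = 0.5, 129 at ρ = 0.7 and 91 at ρ = 0.8.
- ANCOVA, if 20% is the SD of change: the residual variance is 20² × (1 + ρ)/2, so n per arm = 251.2 × (1 + ρ)/2. This gives 189 at ρ = 0.5 and 227 at ρ = 0.8.

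So 128 matches the paired test without further assumptions, and matches a between-arm ANCOVA only under two conditions that the article does not state.

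**2. How often the paired test shows improvement when training adds nothing.** Assumptions, none of them in the document: no true difference between arms, the same mean drift δ in both arms, SD of change 20%. With n = 128, the paired t statistic has noncentrality δ√128/20 on 127 degrees of freedom and is compared with 1.979. For example, at δ = 3 the noncentrality is 3 × 11.314/20 = 1.70.

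| Drift in both arms | IPET arm significantly improved | IPET significant, control not |
|---|---|---|
| 0% | 2.5% | 2% |
| 1% | 8% | 7% |
| 2% | 20% | 16% |
| 3% | 39% | 24% |
| 4% | 61% | 24% |
| 5% | 80% | 16% |

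The middle column counts significance in the direction of improvement only; counting either direction gives 5% at zero drift, about 8.7% at 1%, and the same rounded values from 2% upwards. The last column is p(1 − p), with p the middle column.

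A smaller SD of change raises these figures. If 20% is the cross-sectional SD and ρ = 0.8, the SD of change is 20 × √(2 × 0.2) = 12.6%, and drifts of 2% and 5% give 43% and 99%.

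**3. The between-arm test under the same conditions.** In simulation (128 per arm, SD 20%, ρ = 0.5, which makes the SD of change 20%, no training effect), baseline-adjusted ANCOVA rejected in 4.3, 4.9 and 4.9% of trials at drifts of 0, 2 and 5%. The paired test in the IPET arm showed improvement in 2.7, 20 and 80% of the same trials. The ANCOVA keeps its level because the shared drift cancels.

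**The case against.** The strongest reply is that the valid test is already in the plan. ANCOVA is specified for the primary and the secondary outcomes in the same sentence as the paired t-test, and the study is framed throughout as a randomised controlled trial. A reader might infer that the plan discards the randomisation, or that it makes the within-arm result decisive. The text supports neither: it ranks no test above another. Wording a hypothesis as improvement is also common shorthand for an effect against control. All of this stands, and it limits the fault to a missing hierarchy. It does not remove it, because the paired tests are stated choices at the same threshold, not details left to another document.

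Four further overstatements should be avoided.

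- **McNemar and the primary outcome.** McNemar cannot apply to continuous VO2max. It concerns categorical variables, and its within-arm use is inferred from its being a paired test.
- **Regression to the mean.** This is a weak explanation for VO2max drift, since the eligibility criteria do not select on VO2max.
- **The size of the drift.** The document gives no figure, so no single percentage should be read as the trial's error rate. The discordant pattern can never exceed 25%, the maximum of p(1 − p).
- **The sample size.** A reader might infer that 128 proves the trial was designed around the paired test. It does not: ANCOVA with a cross-sectional SD of 20% and a correlation of about 0.7 leads to nearly the same number.

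**Conclusion.** The point holds as a missing hierarchy, and it should be corrected. The plan places within-arm tests beside the between-arm ANCOVA at one threshold, with hypotheses that do not mention control, and does not say that the ANCOVA decides. The consequence depends on an assumed drift: from 2.5% with none to about 80% at 5%, for an SD of change of 20% and 128 per arm. The direction of the problem does not depend on that assumption, because a within-arm test does not estimate the effect of training against control at any drift.

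The sample size belongs to the same point. If only the between-arm contrast counts, 80% power at 128 per group is not established by what the article states. It is about 51% without adjustment, and close to 80% only with a cross-sectional SD of 20% and ρ of about 0.7.

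**What to change.** - State in the Statistics section that each effect hypothesis is judged only on the between-arm, baseline-adjusted difference with its 95% CI: ANCOVA for continuous outcomes, and a between-arm comparison for categorical ones.
- Report within-arm change descriptively (mean change and SD, or counts), without p-values. This drops the paired t-tests and McNemar tests as tests of outcomes.
- Word the hypotheses on fitness, health risk indicators, strength, musculoskeletal disorders, absence and productivity as differences from the control group.
- Restate the power for the between-arm contrast, saying whether 20% is the SD of VO2max or of its change, and which baseline to follow-up correlation is assumed.

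The first three changes cost wording only and mean fewer tests. The fourth may show a shortfall. Without adjustment, 253 per arm would mean 506/0.7, about 723 recruited at 30% dropout, against the stated target: "With an estimated dropout of 30% the research project has to recruit around 400 employees". Enrolment ran from May 2011 to March 2012 and is closed, so the restated figure would serve to interpret the confidence interval, not to change recruitment.
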